#### **Serious adverse events (SAEs)**

A serious adverse event is any untoward medical occurrence or effect that

- results in death;
- is life threatening (at the time of the event);
- requires hospitalisation or prolongation of existing inpatients' hospitalisation;
- results in persistent or significant disability or incapacity;
- is a congenital anomaly or birth defect; or
- any other important medical event that did not result in any of the outcomes listed above due to medical or surgical intervention but could have been based upon appropriate judgement by the investigator.

An elective hospital admission will not be considered as a serious adverse event.

The use of i.v. iron injection, can cause allergic reaction. This product is used normally for all anaemic patients with iron deficiency with specific surgical indication. In-hospital protocol is already in use. No other or extra care will be undertaken. Addendum describes the in-hospital protocol for the use of i.v. iron injection (in Dutch).

Due to physical exercises patient can have muscle complaints, or even fall. Usual care will be given.

All events will be reported by the investigator (CM) to the sponsor (LLA). Patient will still be included in our database and will not be withdrawn from this study when an adverse event occurs.

To our knowledge no other adverse events might occur when participating in this study.

The investigator will report all SAEs to the sponsor without undue delay after obtaining knowledge of the events, without any exceptions except for the following SAE:

- If death occurs during this study due to the normal cause of illness, we will not notify this as a SAE.

The sponsor (LLA) will report the SAEs through the web portal *ToetsingOnline* to the accredited METC that approved the protocol, within 7 days of first knowledge for SAEs that result in death or are life threatening followed by a period of maximum of 8 days to complete the initial preliminary report. All other SAEs will be reported within a period of maximum 15 days after the sponsor has first knowledge of the serious adverse events.

## 8 STATISTICAL ANALYSIS

Standard procedure will be followed for descriptive statistics. The primary analysis for incidence of delirium will be a logistic regression model with adjustment for prognostically important covariates: age, gender, surgical history, comorbidity, (cardiac, pulmonary, neurological, renal, dementia, diabetes), use of medication, smoking status, use of alcohol, social economic status, use of glasses or hearing impairment, BMI, home situation. We will also consider the POSSUM score and Charlson comorbidity score. Repeated measure analysis will be applied for measurement over time during follow up. Historic and prospective patients will be selected for analysis fulfilling the same set of inclusion criteria. Missing data will be studied for specific patterns of occurrence, and multiply imputed. Statistical analysis was performed with IBM SPSS statistics software (SPSS Inc., Chicago, Illinois, USA).

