## 1. INTRODUCTION AND RATIONALE

The population of people above 65 years old is expected to double in the next 35 years. The increase of age is associated with an increase in need for medical care and number of patients requiring surgery. A higher rate of post-operative complications, like a delirium (37%), longer hospital stay, ICU admission, and mortality is associated with increasing age.[1, 2]

In our hospital, within the population of 70 years or older, approximately 85 patients per year undergo surgery for colorectal cancer and about 50 patients per year undergo surgery for abdominal aortic aneurysm. We expect an increase in the number these surgical procedures performed during the coming years (also due to the implementation of screening programs).

A delirium is often a fatal disorder. It affects as much as 50 % of the elderly people who are hospitalised. In the population described above, the incidence of a delirium is about 15%. The 6-month mortality is increased within patients with a postoperative delirium (20%) versus no delirium (3%). [3] In short a delirium is a common complication after surgical intervention and results in a significant decrease in quality of life, an increased rate of complications, mortality and additionally is associated with high costs. Therefore a delirium holds essential health relevance.

The cause of a delirium can be the result of a single factor but is mostly a combination of different factors at once. Many factors have been identified and validated to be an independent cause of a delirium. These factors of frailty are for example the patient's nutritional state, physical health, the use of medication, the patient's mental state, laboratory results (such as anaemia and renal function), delirium in patient's history, visual and hearing impairment.

At the moment physicians are already more aware of these frail elderly and these factors of frailty but it is only tackled at admission in hospital or at long care facilities. A delirium is preventable in 30 to 40 % of the cases. Therefore the Hospital Elder Life Program (HELP), a worldwide non –pharmaceutical program, is implemented. This program starts at admission and is proven to be effective to prevent a delirium. [3-5] Another recent study, for patients with an acute hip surgery, shows that specific ortho – geriatric care during admission improves the outcome 4 months after surgery. [6]

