The historical patient group is based on patients admitted to the Amphia Hospital Breda in 2013 till November 2015. All data is gathered retrospectively but due to the use of the electronic patient file (Hyperspace Version IU4 (Epic, Inc., Verona, WI)) data was saved prospectively. No recent major changes have been made to indicate new procedures or pathways for the interventional care group compared to the historical patient group. The historical group will be comparable to the interventional care group in age ( $\geq 70$  years), ethnicity, gender and indication for surgery. Patients with emergent or urgent surgical intervention won't be included in this study, neither in the historical cohort. All patient who underwent neo adjuvant chemo – and / or radiotherapy are included.

However no questionnaires are undertaken in the historical group, hence the lack of prospective knowledge concerning dementia (scored by MMSE), quality of life or depression scale.

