**Flowchart Inclusion of patients**

[figure not shown]

We assume to be able to include 275 patients over a period of two years, starting 1 January 2016 until 31 December 2017. About 20% of these patients will be included for an abdominal aortic aneurysm and 80% for gastro –intestinal carcinoma. [1]

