### Inclusion criteria

In order to be eligible to participate in this study, a subject must meet all of the following criteria:

- all patients of 70 or older;
- all Ethnicities;
- male or female;
- patients who will be operated on due to colorectal cancer or abdominal aortic aneurysm;
- only primary surgery, or patients who had abdominal surgery more than one year ago;
- the surgical procedure can be laparoscopic, open or EVAR;
- the surgical procedure can be curative or palliative;
- patient or attorney –in –fact are capable to give written informed consent.

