**Sample size calculation**

To reduce the percentage of delirium from 15% to 7,5%, with a power of 80% with 5% two-sided significance level, a 50 -50 trial, needs 550 patients, or 275 patient per study arm.

We propose to make a comparison to a retrospective control group of patients studied between 2012 and 2014 in the Amphia Hospital, Breda. [1]

We aim to include 275 patients in the prospective study, which is feasible during approximately 2 years of accrual.

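### The primary logistic model adjusts for neither indication nor type of procedure, although the controls are historical and the protocol gives two different aneurysm shares (37% and 20%)

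*Protocol*

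**What the plan says.** Section 8 of the protocol fixes the main analysis: "The primary analysis for incidence of delirium will be a logistic regression model with adjustment for prognostically important covariates". It names age, gender, surgical history, six comorbidities, medication, smoking, alcohol, socioeconomic status, sight or hearing, BMI and living situation. POSSUM and Charlson are only to be considered. Indication and type of operation are absent. Surgical history does not stand in for them: section 6.2 lists it among the baseline characteristics taken at the first clinic visit, so it is not the index operation.

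The population pools both indications and all approaches; under the inclusion criteria "the surgical procedure can be laparoscopic, open or EVAR".

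On case mix the protocol says three things:
- Section 1, hospital volume at age 70 or older: "approximately 85 patients per year undergo surgery for colorectal cancer and about 50 patients per year undergo surgery for abdominal aortic aneurysm".
- The inclusion flowchart text, on the 275 planned patients: "About 20% of these patients will be included for an abdominal aortic aneurysm", with the other 80% having gastro-intestinal carcinoma.
- Section 3: "The historical group will be comparable to the interventional care group in age", a sentence that goes on to claim the same for ethnicity, gender and indication.

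The only mechanism given for that comparability is in section 8: both cohorts are selected by the same inclusion criteria.

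**The concern.** The OUTO patients are compared with earlier patients from the same hospital, not with randomised controls. Covariate adjustment is therefore the main protection against a difference in case mix being read as an effect of the pathway. Shared eligibility criteria make both cohorts draw on the same kinds of patient; they do not make the proportions equal.

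The protocol itself treats indication and procedure as different clinical situations. Under section 6.2, EVAR patients receive neither an epidural nor a PCA pump, whereas the other patients receive one or the other. Iron injection was already standard for anaemic colorectal patients but is new for aneurysm patients, so even the contrast between pathway and control differs by indication. If delirium risk also differs, any shift in the mix between periods passes into the treatment estimate. The control period is itself given in three ways (March 2013 to March 2015, and 2013 to November 2015, in section 3; 2012 to 2014 under the sample size), so the control mix is not pinned down elsewhere.

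**Working it through.** **1. The plan's own figure.** The inputs are "To reduce the percentage of delirium from 15% to 7,5" percent, "with a power of 80% with 5% two-sided significance level", and "needs 550 patients, or 275 patient per study arm". With the unpooled two-proportion formula:

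n = (1.960 + 0.842)² × (0.15 × 0.85 + 0.075 × 0.925) / 0.075² = 274.7, or 275 per group.

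The pooled form gives 278. The sample size reproduces, as an unadjusted calculation. The target effect is 15 − 7.5 = 7.5 points.

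**2. Aneurysm share.**
- From section 1: 50 / (85 + 50) = 50/135 = 37.0%.
- From the flowchart text: 20%, or 0.20 × 275 = 55 patients.
- Gap: 0.370 − 0.200 = 0.170.
- Two years at the section 1 volume: 2 × 135 = 270 patients, close to the planned 275.

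The last line matters. The section 1 volume fits the prospective accrual as well as it fits the controls, so the two shares may be conflicting descriptions of one population rather than of two groups.

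**3. Size, if such a gap lay between the groups.** The false difference is the gap in share times the difference in delirium risk between indications. The protocol gives no risk by indication, so 5 to 15 points is an assumption. The last column takes a control rate of 15%, 275 per group, no true effect, and a shift in the direction that favours OUTO.

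| Assumed risk difference | False difference | Share of 7.5-point target | P(significant benefit), nominal 2.5% |
|---|---|---|---|
| 5 points | 0.170 × 5 = 0.9 | 11% | 4.7% |
| 10 points | 0.170 × 10 = 1.7 | 23% | 8.3% |
| 15 points | 0.170 × 15 = 2.6 | 34% | 14% |

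The sign is unknown. Holding controls at 15% overall with 37% aneurysm patients, and OUTO at 20%, the expected OUTO rate without any effect is 16.6% if aneurysm patients have half the colorectal risk, 15.0% if the risks are equal and 13.1% if they have twice the risk. The first hides benefit; the last imitates it. All of these figures ignore the other covariates.

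**4. Room in the model.**
- Expected events at the target effect: 275 × 0.15 + 275 × 0.075 = 41.25 + 20.63 = 61.9.
- Expected events with no effect: 2 × 41.25 = 82.5.
- Parameters at one per item: 3 (age, gender, surgical history) + 6 comorbidities + 7 others = 16, plus the group term = 17.
- Events per parameter at the target effect: 61.9/17 = 3.6.
- With one added term: 61.9/18 = 3.4. With three: 61.9/20 = 3.1.

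**The case against.** The strongest objection is that 37% against 20% is not a contrast between the two study groups. Section 1 gives hospital volume, not the composition of the control cohort, and that volume matches the OUTO accrual just as well. The flowchart text supports its 20/80 split with the same cited study that the sample size section cites for the control group, so the 20% may describe the controls. This stands. A reader might infer that the protocol shows a 17-point imbalance, or a 14% false-positive risk; it shows neither. Those figures are the upper end of an illustration.

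Two further points stand. Part of any indication effect may be absorbed by gender, smoking, cardiac comorbidity and medication, which are in the model. And section 1 expects growth in these operations generally, without saying that one indication will grow faster, so it is no evidence of a shift in mix.

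A second tempting reading is that the list is so long for 62 events that the primary estimate is materially overfitted and should be cut to a short penalised model. The size does not bear this out. In simulation, going from 5 to 16–18 covariates moved the mean log odds ratio from −0.80 to between −0.83 and −0.84 (true value −0.78), against a sampling standard deviation of 0.32, and type I error stayed at about 5–6%. Cutting would also remove factors such as impaired sight and hearing and nutritional state, which section 1 counts among the independent causes of delirium. In a non-randomised comparison that trade is debatable.

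It might also be said that a statistical analysis plan could add the terms. But the protocol does not leave the list open; it writes it out, without these two factors. None of these objections supplies a reason to leave them out.

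**Conclusion.** The point holds in a limited form and should be fixed. The protocol names the adjustment set for a non-randomised primary comparison and omits the two factors that most plainly define case mix in this population. Its claim that the groups will be comparable in indication has no mechanism behind it, and its own two aneurysm shares disagree.

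Whether the groups will in fact differ cannot be told from the document. The size of 0.9 to 2.6 points, 11–34% of the target effect, rests on two assumptions: that the 17-point gap lies between the groups, and that delirium risk differs by 5 to 15 points between indications. The direction is unknown, and the other covariates may reduce the bias. The case for change rests on the omission and its low cost, not on a demonstrated bias.

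**What to change.** - Add indication and type of procedure, as recorded in both cohorts, to the covariates of the primary model in section 8. This can be one factor with levels for colorectal laparoscopic, colorectal open, EVAR and open aneurysm repair. With only about 55 aneurysm patients planned, state in advance that sparse aneurysm cells will be collapsed. Use the procedure as recorded, since the protocol does not say that the approach planned before surgery is available, least of all for the historical cohort.
- Reconcile the aneurysm shares in section 1 and the flowchart text, and report the observed share in each group.
- Do not enter Charlson alongside the separate comorbidity terms that it overlaps.

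The cost is wording plus one to three parameters, which lowers events per parameter from 3.6 to between 3.4 and 3.1 at the target effect. Leaving Charlson out of the model limits this. No new prospective data are needed: indication defines eligibility, and section 6.2 already provides for collecting data on the procedure.

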### 3. STUDY DESIGN

This study will be a prospective interventional study, starting 1 January 2016, and planned until 31 December 2017.

A pre-operative clinical pathway is set up for patients of seventy years or older with surgical indication for colorectal cancer or abdominal aortic aneurysm, the 70 PLUS outpatient clinic in our surgery department. Within one week since indication for surgery is decided, a nurse practitioner, a physiotherapist and a dietician will see these patients and all factors of frailty will be investigated. If needed, a geriatrician will also see the patient for complete geriatric assessment and advice during admission to prevent delirium (criteria for CGA is described in *chapter 6.2 study procedures*). Diet advice and physical exercises will be given to all patients in need. Patients must follow these advices and keep a diary.

All patients aged  $\geq 70$  years will be included in this study to follow our pre-operative clinical pathway for optimisation. Also patients, who are not clinically fit to wait for 5 weeks will be included and optimised until surgery.

We propose an optimum preparation time during 5 to 6 weeks till surgery. This is based on the SONCOS quality guidelines 2015 for colorectal cancer, in which a maximum delay of 6 weeks is proposed from pathology result until surgery (Addendum: SONCOS quality guidelines 2015 for colorectal cancer ).

Prospectively gathered data of all cases will be compared to a retrospective, historical, control group of comparable patients from 1 March 2013 till 1 March 2015.

These patients have not been evaluated for factors of frailty in advance. This is a cohort of patients of the age  $\geq 70$  years who received treatment for colorectal cancer with or without neo-adjuvant therapy (radiation or chemotherapy). Both open and laparoscopic surgery will be included.

Also patient who received treatment for abdominal aneurysm of the age  $\geq 70$  are included. These patients underwent an EVAR or open repair. (Complete description of the pathway in the retrospective group is described in *chapter 6.2 Study procedure* and addendum *Amphia protocol Colonchirurgie*)

Only electively planned surgery is included, all emergent or urgent surgical procedures are excluded.

Data of patients in both groups will be gathered in the Amphia Hospital Breda, the Netherlands.

All information will be gathered using Hyperspace Version IU4 (Epic, Inc., Verona, WI).

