Anaemic patients (haemoglobuline level of < 7.4 mmol/L(<120 g/L) for women and < 8.1 mmol/L for men (<130 g/L)) will be given iron–injection after they filled in the WHOQOL-Bref. These patients will be admitted at day-care, which is standard care for all patients operated on with anaemia. [21] For the patients operated on in case of abdominal aortic aneurysm iron-Injection is part of this new pre – operative pathway and not former standard care.

Dietician is consulted when patient lost weight without purpose or lost appetite.

Nutrition is quantified using BMI, the minimal nutritional assessment test (MNA) and SNAQ -RC score. Also prealbumine is tested in the laboratory results.

Complete geriatric assessment is done for patients with the following criteria:

- MMSE score < 24 points;
- MMSE score < 26, If patient went to secondary school or university;
- delirium in medical history;
- polypharmacy:
  - Colorectal patients with more than 4 different kinds of medication
  - Vascular patients with more than four different kind of medication next to regular vascular preventive medication (Anti-coagulants, a statin, or bloodpressure medication)
- Time –up and Go Test (TUG Test) of ≥ 15 seconds.

Geriatrician will assess if preventive medication, like Haloperidol, is necessary.

The Care giver strain index (CSI) will be used to investigate pressure of first care giver during the course of illness of the patient.

At hospital admission (T2) patients will be seen by the same physiotherapist and researcher.

The physiotherapist will assess patients' condition and function using the TUG test, MIP, and 10 meters walk test.

The same laboratory results will be measured. The outcome of the WHOQOL–Bref can be aberrant if patients endure depressive feelings. This is why we will screen for depression, using

CES D-16 questionnaire at admission.

During admission a physician will see all patients on a daily basis. A nurse, while providing regular daily care, will screen for a delirium using the Delirium Observation Screening Score (DOSS) three times a day. DOSS is a shortened version with 13 items and is scored three times a day. A delirium is highly presumable if the patient had a DOSS of  $\geq 3$  and scored three times in a row. When delirium is suspected a geriatrician will be consulted to confirm the diagnosis using the DSM-IV criteria. [10] Also nurses will daily examine the level of pain using the Visual Analogue Score (VAS).

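### The primary logistic model omits history of delirium and baseline haemoglobin, which the protocol itself names as causes of delirium, and so leaves the historical-control comparison open to confounding by them

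*Protocol*

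**What the plan says.** Section 3 (Study design) sets up a non-randomised comparison: "Prospectively gathered data of all cases will be compared to a retrospective, historical, control group of comparable patients". It describes the two groups as comparable in age, ethnicity, gender and indication.

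Section 8 makes an adjusted logistic regression the primary analysis and lists its covariates: age, gender, surgical history, six comorbidities (cardiac, pulmonary, neurological, renal, dementia, diabetes), then "use of medication, smoking status, use of alcohol, social economic status, use of glasses or hearing impairment, BMI, home situation". POSSUM and Charlson scores are only to be considered.

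Section 1 lists factors that it describes as validated independent causes of delirium. The list includes "laboratory results (such as anaemia and renal function), delirium in patient's history, visual and hearing impairment".

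Section 6.2 (OUTO Care) uses "delirium in medical history" as one criterion for a complete geriatric assessment, includes haemoglobin among the study laboratory results, and makes anaemia the trigger for iron.

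For the controls, section 3 says that nobody assessed frailty factors in advance, but that through the electronic patient file "data was saved prospectively". It names questionnaire-based items (dementia by MMSE, quality of life, depression) as lacking.

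**The concern.** In a historical-control study, shared inclusion criteria and covariate adjustment are the only protections this protocol offers against differences in case mix. Section 8 carries over renal disease and sensory impairment from the section 1 list, but not delirium history or anaemia.

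The section 8 list closely follows the first baseline list in section 6.2. Delirium history and haemoglobin stand further down in that section, under the geriatric-assessment criteria and the laboratory results. The omission therefore looks like an oversight rather than a choice.

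Both factors also steer the intervention, since one triggers geriatric assessment and the other triggers iron. A reader of the results will want to know whether the cohorts were alike on exactly these two. If they were not, the model as listed has no term to remove the difference.

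An unseen analysis plan does not answer the point, because the protocol fixes the list itself. Nothing else in the protocol repairs it: sections 6.1 and 8.3 relate frailty factors to delirium but do not adjust the group contrast.

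**Working it through.** **1. The plan's own figure.** The sample size section gives 15% versus 7.5%, "with a power of 80% with 5% two-sided significance level", and concludes that a 50-50 trial "needs 550 patients, or 275 patient per study arm". With unpooled variance:

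n = (1.960 + 0.842)² × (0.15×0.85 + 0.075×0.925) / 0.075² = 274.7, so 275 per group.

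The pooled-variance formula gives 278. The stated figure reproduces and this point does not change it. The planned odds ratio is (0.075/0.925)/(0.15/0.85) = 0.46.

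**2. Possible bias.** From the protocol: control risk 15%, planned fall 7.5 points. Not in the protocol, and therefore assumed: the prevalence of each factor in each cohort and its odds ratio (OR) for delirium.

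Let p_C and p_T be the prevalence in controls and OUTO patients, and let expit(x) = 1/(1+e^(−x)). Find the intercept a such that

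(1−p_C)·expit(a) + p_C·expit(a + ln OR) = 0.15.

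Then put p_T in place of p_C, with no treatment effect. The distance of the result from 15% is the spurious effect.

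Example: p_C = 10%, p_T = 5%, OR 4. The intercept gives risks of 12.6% without and 36.6% with previous delirium (0.90×12.6 + 0.10×36.6 = 15.0). In OUTO patients 0.95×12.6 + 0.05×36.6 = 13.8%, a spurious fall of 1.2 points.

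| Factor | Controls vs OUTO | OR | OUTO risk, no true effect | Spurious change (points) |
|---|---|---|---|---|
| Delirium history | 10% vs 10% | any | 15.0% | 0 |
| Delirium history | 10% vs 8% | 4 | 14.5% | −0.5 |
| Delirium history | 15% vs 10% | 3 | 14.1% | −0.9 |
| Delirium history | 10% vs 5% | 4 | 13.8% | −1.2 |
| Delirium history | 15% vs 5% | 4 | 12.7% | −2.3 |
| Delirium history | 15% vs 5% | 6 | 11.9% | −3.1 |
| Delirium history | 5% vs 15% | 4 | 17.5% | +2.5 |
| Anaemia | 40% vs 30% | 1.5 | 14.5% | −0.5 |
| Anaemia | 50% vs 40% | 2 | 14.1% | −0.9 |
| Anaemia | 50% vs 30% | 3 | 12.4% | −2.6 |

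Both factors together, taken as independent:
- Moderate case (history 15% vs 10%, OR 3; anaemia 50% vs 40%, OR 2): 1.7 points, spurious odds ratio 0.87.
- Extreme case (history 20% vs 10%, OR 5; anaemia 50% vs 30%, OR 3): 4.6 points, spurious odds ratio 0.66.

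**3. Room in the model.** Expected events: 275×0.15 + 275×0.075 = 61.9, about 62. Counting one parameter per item gives group 1, age 1, gender 1, surgical history 1, comorbidities 6, and the seven items from medication to home situation 7, so at least 17. Events per parameter: 61.9/17 = 3.6. With two more terms it is 61.9/19 = 3.3; with POSSUM and Charlson as well, 61.9/21 = 2.9.

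**4. Power.** With balanced cohorts, simulation at 275 per group showed gains of only 1 to 3 points from adjusting for previous delirium. The case rests on bias, not power.

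**The case against.** A reader might infer that the comparison is confounded. The protocol does not show that. Bias needs a difference in prevalence between cohorts and none is reported; both come from one hospital with the same indications and inclusion criteria. With 275 per group and prevalence near 10%, the chance standard error of a difference is √(2×0.10×0.90/275) = 2.6 points. A gap of 10% vs 5% is then about 2 standard errors and 15% vs 5% nearly 4, so the larger rows need a systematic cohort difference. The calculation also ignores the listed covariates; so far as age, dementia or neurological disease go with past delirium, the residual bias would be smaller. All of this stands, and limits the point to an open route for bias.

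A reader might also infer that both factors are on record for everyone. Collection is shown only for OUTO patients. The electronic file makes it plausible for controls but does not prove it, and unequal recording could itself add bias. This stands, and the fix must include a check.

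It may be tempting to make room by dropping smoking, alcohol or socio-economic status because section 1 does not mention them. That fails: section 1 gives examples only, and section 6.2 includes all three in its list of baseline characteristics and predictors of delirium.

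Finally, the model is already crowded. This is true, but it is a reason to handle the list with care, not to leave out two factors that the protocol itself calls causes.

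**Conclusion.** The point holds as a low-cost improvement. The covariate list omits two factors that the protocol names as independent causes of delirium and collects in the OUTO group, and nothing else in the protocol adjusts the group contrast for them. The OUTO effect is therefore left open to confounding that could either imitate or hide a benefit.

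The size is unknown. Under the assumed inputs it is about 0.5 to 3 points per factor, or 6% (0.48/7.5) to 41% (3.07/7.5) of the planned fall, and zero if the cohorts are balanced. In no scenario examined does either factor alone, or both together, account for the full 7.5 points. The stated sample size is unaffected.

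**What to change.** In section 8, add to the named covariates of the primary model:
- history of delirium (yes/no);
- haemoglobin from the diagnostic work-up, before any iron is given. The value at admission comes after the intervention, and adjusting for it could remove part of the OUTO effect.

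Take both, in both cohorts, from the electronic patient file as recorded before the surgical indication, so that history is not ascertained by interview in one group and by chart in the other. Confirm first that the control files hold both items, and report how complete they are by cohort. Keep smoking, alcohol and socio-economic status unless there is a reason other than their absence from section 1.

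The cost is extraction of two chart items for the controls and two more parameters (3.6 falling to 3.3 events per parameter). Penalised regression or a propensity score can absorb the latter, and the choice should be stated in advance. The remaining weakness is possible under-recording of past delirium in control files.
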